### Process evaluation

After the intervention, a process evaluation will be performed amongst participating midwives and respondents. In the process evaluation midwives will be asked under what conditions they would be willing to provide this type of intervention themselves. It will be assessed also whether and under what circumstances assistants, present in some practices, can execute the intervention program.

It is likely that practices who are interested in participating in a study about weight gain during pregnancy are practices that are already paying more attention to this subject more compared to other practices. In order to identify such differences between participating and non-participating practices, questions about the time spent by midwifes on subjects related to weight gain or lifestyle are incorporated.

Furthermore, 50 subjects will be asked how they experienced the intervention, and which factors influenced success or failure of the intervention. Also 50 women from the control group will be asked about the regular care, received from the midwives during pregnancy. The results of the process evaluation will be used to facilitate future implementation.

### Statistical analyses

Analyses will be performed to estimate the effect of the intervention on five domains: 1) total weight gain during pregnancy 2) the percentage of women gaining weight above the recommended IOM guidelines; 3) weight retention at six months and one year postpartum; 4) physical activity levels; and 5) behavioral determinants of weight management, physical activity and nutrition.

Longitudinal logistic regression analysis will be used for dichotomous outcome measures, and longitudinal linear regression analyses will be performed for all other outcome measures. In these analyses, the correlation between multiple measurements within one individual is taken into account. The regression coefficient reflects the average difference in the outcome variable between conditions. Possible confounders will be entered into the regression analyses. Confounding will be defined as a change in the regression coefficient of 10% or more. Possible effect modification will be studied as well, defined as a significant (p <0.10) interaction-term between group allocation and the variable concerned. Datawill be analysed according to the intention-to-treat principle and the per protocol principle.

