**Methods:**

The effectiveness of the New Life(style) intervention program versus usual care by midwives is evaluated in a randomised controlled trial. Women who expect their first child and visit one of the participating midwifery practices are included. The intervention is standardised in a protocol and executed by trained counsellors with the women who are randomised in the intervention group. During 5 sessions – at 18, 22, 30 and 36 weeks of pregnancy and at 8 weeks postpartum – individual weight gain is discussed in relation to weight gain guidelines for pregnant women of the American Institute of Medicine. Counsellors coach the women to maintain or optimise a healthy lifestyle, in a period of drastic physical and mental changes. Data is collected at 15, 25, 35 weeks of pregnancy and at 6, 26, and 52 weeks after delivery. Primary outcome measures are body weight, BMI, and skinfold thickness. Secondary outcome measures include physical activity, nutrition and blood levels of factors that are associated with energy homeostasis.

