### Study population

#### Sample size

The aim is to include 275 participants in the study. A power analysis has been based on the effects of the intervention program on BMI of participants in the intervention group. In order to be able to detect a clinically relevant difference in BMI of 0.8 kg/m^2 ^at six months postpartum between the intervention and control group, 220 participants are needed, 110 participants in each group. These numbers are based on a power (1-B) of 0.80, a significance level of 5% (two-sided) and a standard deviation of 2.0 kg/m^2^. When a drop out of 20% is taken into account, which is normal for similar research with 1 year follow up, 275 women are needed for this trial.

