### Primary outcome measures

#### Body weight and BMI

Body height is measured on bare feet by means of a wall-mounted height scale (SECA 206), with an accuracy of 0.1 cm. Calibrated electronic scales (SECA 888) are used to determine body weight of the participants in underwear and pants, with an accuracy of 0.1 kg. Both weight and height is measured twice, and the mean value of the two measurements is computed and used to calculate individual body mass index (BMI, kg/m^2^) at 26 and 52 weeks after pregnancy. Pre-pregnancy BMI is based on self reported pre-pregnancy weight.

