### Skinfold thickness and percentage body fat

A Harpenden calliper is used to assess skinfold thickness of the following four skinfolds: biceps, triceps, subscapular and suprailiac, according to the method described by Weiner and Lourie [27]. All skinfolds are assessed twice. A mean value of the two is computed. In case the two measurements of a skin fold differ more than 1.0 mm, the skin fold is measured a third time and the mean value of the three values is calculated.

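### The declared primary outcomes, the outcome the trial is sized for and the five analysis domains are three different sets, and none of the domains names the powered outcome, BMI at six months postpartum

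*Protocol article*

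**What the plan says.** The protocol article describes what the trial tests in three places.

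- **Declared primary outcomes.** The abstract (Methods) says "Primary outcome measures are body weight, BMI, and skinfold thickness". No order is given. Under Body weight and BMI, the weight and height measurements are "used to calculate individual body mass index (BMI, kg/m^2^) at 26 and 52 weeks after pregnancy". Under Skinfold thickness and percentage body fat, still within the primary outcomes, four skinfold sites are measured.
- **Powered outcome.** Sample size says "A power analysis has been based on the effects of the intervention program on BMI of participants in the intervention group". The target is a "clinically relevant difference in BMI of 0.8" kg/m² at six months postpartum, with "a standard deviation of 2.0" kg/m², 80% power and a two-sided 5% level. This gives 110 per group, 220 in all, and 275 after 20% dropout.
- **Analysis targets.** Statistical analyses says "Analyses will be performed to estimate the effect of the intervention on five domains". These are total pregnancy weight gain, the percentage of women above the IOM limits, weight retention at six months and one year, physical activity, and behavioural determinants.

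The analysis section then assigns longitudinal logistic regression to dichotomous outcomes and longitudinal linear regression to all others. It describes the regression coefficient as the average difference between the groups.

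**The concern.** A trial should give one answer to the question of which result decides whether the programme works. Here the three places give three answers, and no section names the deciding outcome or visit. The outcome that justifies the number of women is not among the named analyses. Conversely, the percentage above the IOM limits is a named analysis but appears in no outcome list, and physical activity, a secondary outcome, stands in the same list as the weight domains.

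The stakes are practical. The Discussion makes an update of Dutch or international midwifery guidelines depend on the programme proving effective. If the deciding outcome is settled only after results are known, several weight-related results compete for that role, while the sample size was worked out for one of them at one visit.

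**Working it through.** **1. The three sets side by side**

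| Outcome | Declared primary | Powered | Named domain |
|---|---|---|---|
| BMI, six months (26 weeks) | yes | yes | no |
| BMI, 52 weeks | yes | no | no |
| Body weight | yes | no | indirectly (gain, retention) |
| Skinfold thickness | yes | no | no |
| Percentage above IOM limits | no | no | yes |
| Physical activity | no (secondary) | no | yes |
| Behavioural determinants | no | no | yes |

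The powered outcome has no entry in the last column.

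**2. What the general regression sentence delivers**

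BMI and skinfolds are continuous outcome measures, so the sentence on longitudinal linear regression can cover them. The coefficient it describes is an average difference. With BMI calculated at 26 and 52 weeks, that is an average over both visits, whereas Sample size is for the difference at six months. The two agree only if the effect is the same at both visits.

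**3. The sample size**

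Inputs, all from Sample size: difference 0.8, SD 2.0, two-sided 5%, power 80%.

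n per group = 2 × [SD × (z₀.₉₇₅ + z₀.₈₀) / difference]² = 2 × [2.0 × (1.960 + 0.842) / 0.8]² = 98.1, so 99 per group and 198 in all. A t-test version gives 100 per group.

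The stated 110 per group is not reproduced; it is about 11% higher, which is the safe direction. The dropout step reproduces: 220 / 0.80 = 275.

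Power at 110 per group: the standardised difference is 0.8 / 2.0 = 0.4, and 0.4 × √(110/2) = 2.966. Power = Φ(2.966 − 1.960) = 84.3%.

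**4. Power if the level were split**

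Assumption: every primary outcome has the same 0.4 SD effect as BMI. The article gives no effect sizes for the others.

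| Tests | Bonferroni level | Critical z | Power at 110 per group | n per group for 80% | Total with 20% dropout |
|---|---|---|---|---|---|
| 1 | 0.05 | 1.960 | 84.3% | 99 | 248 |
| 3 | 0.0167 | 2.394 | 71.7% | 131 | 328 |
| 6 | 0.0083 | 2.638 | 62.9% | 152 | 380 |

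**5. False-positive chance if each test were done at 5%**

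Independent tests give the upper figures: 1 − 0.95³ = 14.3% for three and 1 − 0.95⁶ = 26.5% for six. The outcomes are correlated, so the true values are lower. For k two-sided z-tests with a common correlation r (assumed, since the article gives none):

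| k | r = 0.5 | r = 0.7 | r = 0.9 |
|---|---|---|---|
| 3 (one per primary outcome) | 12.5% | 10.9% | 8.4% |
| 6 (three outcomes, two visits) | 20.7% | 16.4% | 10.8% |

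A more realistic pattern sets weight with BMI at 0.90 to 0.95 and skinfolds with either at 0.6 to 0.8. That gives about 9% to 10% for three tests. Adding a correlation of 0.8 to 0.9 between visits gives about 12% to 16% for six.

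**The case against.** **A reader might infer that BMI and skinfolds are never analysed, and that the powered comparison is never tested.** The text does not support this. The sentence applying longitudinal linear regression to all remaining outcome measures can include them. What can be said is that they are in none of the five named domains, and that the sentence does not specify the six-month contrast.

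**BMI is partly present in substance.** Weight retention is assessed at six months and one year, the same times at which BMI is calculated, and an adult's height is fixed. This is fair. But retention is a change in weight and BMI is a level, so the powered comparison is approached and not stated. Skinfolds have no such counterpart.

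**A reader might infer that the plan tests several primaries at a shared 5%.** The article does not say so. The 5% belongs to the sample-size calculation, and a multiplicity rule may stand in an analysis plan that is not shown. Its absence here is no fault. The error rates above are therefore conditional on testing each outcome at 5%.

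**The inflation can be exaggerated.** The 20.7% needs six separate tests and a uniform correlation of 0.5, which is implausibly low for weight and BMI. A longitudinal model with one coefficient per outcome points to three tests. This objection stands, and the lower ranges are the ones to use.

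**A hierarchy or a multiplicity rule would also cure the problem, and the programme's stated focus is weight gain within the IOM limits.** Both points are true. However, splitting the level over three outcomes drops power at the planned size to about 72%, and the article gives no sample-size basis for pregnancy gain. BMI at six months is the only outcome for which the 275 is justified.

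**Conclusion.** The point holds as a contradiction within the article. Three unranked primaries, one powered outcome at one visit, and five domains that name neither BMI nor skinfolds cannot all describe the same main question. This does not depend on any unseen document.

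Its size depends on assumptions. If each of the three primaries were tested at 5%, the chance of at least one false positive would be about 8% to 13% for correlations from 0.9 down to 0.5. For six tests it would be about 11% to 16% for correlations from 0.9 down to 0.7. Both are clearly above 5%, though not extreme. The planned 110 per group supports one test at two-sided 5% (84% power) but not three with a Bonferroni split (about 72%, assuming 0.4 SD for each).

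**What to change.** - In the abstract and under Body weight and BMI, name BMI at 26 weeks postpartum as the single primary outcome, since Sample size is built on it.
- In Statistical analyses, list it first, as the difference between groups at that visit taken from the longitudinal model (for example through a group-by-time term), not as the average over visits. Rest the claim of effectiveness on this contrast.
- List body weight, skinfold thickness, the 52-week values, pregnancy weight gain and the percentage above the IOM limits as secondary. List physical activity and behavioural determinants as supportive.

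The change is wording only. It needs no further data and no more women, because about 99 to 100 per group suffice and 110 are planned. It should be made before results by group are seen. The cost is that a positive finding on another weight measure alone would no longer support the main claim.

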## Background

Over 1.1 billion adults and 10% of children worldwide are now classified as overweight or obese [1]. Because of a substantial adverse impact on health and well-being [2], stabilising or decreasing the number of people with overweight is addressed as a target of many regional and national health programs in developed countries [3]. As different life events can trigger a shift in the energy balance resulting in positive weight changes and a higher risk of developing overweight, these moments are thought to be the moments when people will benefit most from health-promoting activities. Therefore, subgroups such as children who are starting school, retired or sick people, are often the target group of health promoting programs [4].

In this manuscript we elaborate on the New Life(style) project. In this study the focus is on pregnant women, because pregnancy has shown to be an independent risk factor for developing overweight [5-8]. Although the American Institute of Medicine (IOM) developed evidence based guidelines for weight development during pregnancy in 1990, still 20% to 40% of women gain more weight than advised by the IOM [9]. Weight gain during pregnancy is considered to be the most important determinant of postpartum weight retention [10,11]. Studies describe an average weight retention of 2–3 kg, 6 to 12 months after delivery and losing this "extra" weight after having given birth proves to be difficult [12,13]. For this reason, preventing excessive weight gain during pregnancy is important in the prevention of overweight and obesity among women of childbearing age.

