### Randomisation

A computerized random number generator draws up an allocation schedule prestratified for midwifery practice; within practices respondents are allocated to the intervention group or to the control group at random. During the first telephone call with the research assistants – 2 weeks after the first appointment with the midwife; at 10–14 weeks of pregnancy – participants are informed about which group they are assigned to.

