### Blood samples

In order to study the influence of lifestyle factors on energy homeostasis and weight gain, blood samples are taken intravenously from a subgroup of participants during each measurement. The midwives also take a blood sample from the umbilical cord. Blood is processed and stored at the laboratory of the VU University Medical Centre, so that – after selecting subgroups of normal and high gainers – blood levels of leptin, ghrelin, fasting insulin/glucose, insulin growth factor 1, insulin growth factor binding protein 1 and 3, and cortisol can be measured.

By means of the questionnaires, data are also collected on: perceived health, stage of change with regard to weight management, physical activity and diet according to the model of Prochaska, and behavioral determinants such as attitude, social support, self efficacy with regard to weight management, physical activity and nutrition. Possible confounders that are assessed include: age, age at menarche, education, ethnicity, marital status, smoking behaviour and individual health status, including complications during pregnancy, the duration of labour and possible complications during or after delivery.

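### For the percentage of women above the IOM guidelines, the logistic coefficient is not an average difference, and the 10% change rule can report confounding where there is none

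*Protocol article*

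**What the plan says.** In the protocol article, Statistical analyses, the second of five effect domains is "the percentage of women gaining weight above the recommended IOM guidelines". On the model, the section says "Longitudinal logistic regression analysis will be used for dichotomous outcome measures", with longitudinal linear regression for every other outcome. It then explains the estimate once, for both model types: "The regression coefficient reflects the average difference in the outcome variable between conditions". It goes on to adjustment: possible confounders are entered, and "Confounding will be defined as a change in the regression coefficient of 10% or more". This rule is also not limited to one type of model.

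The candidates are listed under Blood samples: "Possible confounders that are assessed include: age, age at menarche, education, ethnicity, marital status, smoking behaviour and individual health status", followed by complications and duration of labour. Under Randomisation, allocation is individual: "within practices respondents are allocated to the intervention group or to the control group at random". No odds ratio, risk difference or marginal effect is mentioned anywhere for the dichotomous outcome.

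**The concern.** There are two faults, both in what the text states.

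1. **Meaning of the coefficient.** A logistic coefficient is a difference in log odds. It is not an average difference in the outcome, so the only interpretation the plan gives for this domain is incorrect.

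2. **The 10% rule on that coefficient.** The rule treats any sizeable shift after adjustment as evidence of confounding. For an odds ratio this inference fails. Adjusting for a prognostic covariate moves the log odds ratio away from zero even when the covariate has the same distribution in both arms. Within-practice randomisation means that baseline covariates are not expected to confound systematically, so a shift cannot be read as bias removed.

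At stake is which odds ratio gets reported. Its size would depend on which covariates the data happen to admit, and the non-collapsibility part of the shift always goes towards a larger-looking effect.

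**Working it through.** **Inputs.** The background rate of gain above the IOM limits comes from the article's Background: "still 20% to 40% of women gain more weight than advised by the IOM". The 110 women per arm come from Sample size. Intervention-arm rates and covariate strengths are not in the document; they are assumptions and are shown as ranges. The plan gives no figure for this outcome that could be reproduced.

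**Step 1: scale.** Coefficient = ln[p1/(1−p1)] − ln[p0/(1−p0)], with p0 the control rate and p1 the intervention rate.

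| Control v intervention | Difference in percentages | Coefficient | Odds ratio |
|---|---|---|---|
| 40% v 25% | −15 points | −0.69 | 0.50 |
| 30% v 20% | −10 points | −0.54 | 0.58 |
| 20% v 10% | −10 points | −0.81 | 0.44 |

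The last two rows have the same average difference and different coefficients, so the coefficient cannot be that difference.

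**Step 2: shift with no confounding.** Let X be standard normal with the same distribution in both arms, and g the log of its odds ratio per SD. For each arm, solve for the intercept a such that the mean over X of 1/(1+exp(−a−gX)) equals that arm's rate. The adjusted coefficient is a1 − a0. The table shows its change from the unadjusted coefficient.

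| Covariate | 40% v 25% | 30% v 20% | 20% v 10% |
|---|---|---|---|
| Normal, OR 1.5 per SD | +3.5% | +3.0% | +2.1% |
| Normal, OR 2.0 per SD | +9.7% | +8.6% | +6.1% |
| Normal, OR 2.5 per SD | +16.3% | +14.6% | +10.7% |
| Normal, OR 3.0 per SD | +22.5% | +20.3% | +15.4% |
| OR per SD at which the shift reaches 10% | 2.02 | 2.12 | 2.42 |
| Binary (30% or 50% prevalence), OR 2 | +2.4 to +2.6% | +2.1 to +2.2% | +1.4 to +1.5% |
| Binary (30% or 50% prevalence), OR 3 | +6.3 to +6.5% | +5.4 to +5.6% | +3.4 to +3.9% |

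The difference in percentages is fixed by construction in every column.

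**Step 3: several modest covariates together.** Five independent normal covariates at OR 1.5 per SD have a combined log odds ratio per SD of √5 × ln 1.5 = 2.236 × 0.405 = 0.907, an odds ratio of about 2.5. Entered together they shift the coefficient by +16.0%, +14.3% and +10.5% for the three pairs of rates.

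**Step 4: how often the rule fires in a trial of this size (40% v 25%, 220 women).**

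- With the covariate exactly balanced and OR 2.0, 2.5 or 3.0 per SD, the rule flagged confounding on the logistic coefficient in 47%, 88% and 97% of simulated trials. On the risk-difference scale it did so in 1% or less.
- With ordinary randomisation, 110 per arm, it fired on the logistic coefficient in about 29% of trials at OR 1.5 per SD and 62% at OR 2.2. Judged on the standardised difference in percentages, it still fired in about 24% and 48%. Repeat runs differ by a point or two.

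The first result isolates non-collapsibility. The second shows that chance imbalance accounts for much of the triggering in practice.

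**The case against.** The interpretive sentence comes straight after the linear models, is correct for them, and may be a one-line gloss in a condensed article. Nothing suggests that a log odds ratio would be reported as percentage points, since a logistic model is customarily reported as an odds ratio. This stands as a reason to treat the first fault as a correction of wording. It does not remove the fault, because the sentence is unrestricted and no other interpretation is offered.

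A reader might infer that the plan defines this effect as a difference in percentages and so contradicts itself. The document does not go that far: it never says the effect on this domain is a difference in percentages. Whether to lead with an odds ratio or a risk difference is largely a matter of preference.

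A reader might also infer that any baseline covariate on the list, such as age, education or smoking, would set off the rule. The document gives no strengths for these covariates. Several are categorical, and the table above shows that a single weak or binary covariate stays below 10%. The text does not say whether covariates are tested singly or jointly, so the five-covariate case is possible but not certain.

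Finally, the covariate-adjusted odds ratio is a valid quantity, and its standard error grows with adjustment. In simulation, significance barely changed at OR 1.5 per SD (67% unadjusted, 68% adjusted) and rose modestly at OR 2.2 (65% and 70%). The harm is a data-dependent choice of estimate and a misread size of effect. It is not a serious inflation of significance.

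**Conclusion.** Both faults hold, at limited size. The stated meaning of the coefficient is wrong for the percentage above the IOM guidelines. The 10% rule is unsuitable for that coefficient: with no confounding at all it is met by one balanced covariate at an odds ratio of about 2.0 to 2.4 per SD, or by five at 1.5 per SD entered together. Below that strength, non-collapsibility alone does not trigger it.

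Non-collapsibility is not the rule's only weakness, nor necessarily its main one. Because chance imbalance trips it on the risk-difference scale too, keeping the rule and merely changing scale would not be a repair.

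These sizes rest on assumed intervention rates and covariate strengths; only the 20% to 40% background rate and the 110 per arm come from the article. The point is minor to moderate. The primary outcomes are body weight, BMI and skinfold thickness, which are analysed linearly, and for them the quoted interpretation is correct.

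**What to change.** In Statistical analyses:

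- Limit the average-difference interpretation to the linear models. State that the logistic coefficient is a log odds ratio, reported as an odds ratio with its 95% CI. A difference in percentages, standardised over the trial population from the fitted model, may be given alongside.
- Drop the 10% change-in-coefficient rule as the way of choosing covariates. Adjust for one fixed set of baseline covariates, named before the data are examined.

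The cost is a few sentences of wording and, if the optional difference is reported, a routine post-estimation step. No new data are needed. The downside is that a habitual rule is given up and the covariates must be chosen in advance.

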### Intervention

The New life(style) intervention program consists of 5 individual counselling modules together with a general information brochure. In the modules the counsellors discuss with the women allocated to the intervention group, how to control their weight during and after pregnancy, and how to maintain or optimize a healthy lifestyle in a period of drastic physical and mental changes. Women go through these counselling sessions in 30 weeks; they have appointments with their counsellor at 18, 22, 30 and 36 weeks of pregnancy and at 8 weeks postpartum. The counsellors, in charge of these counselling sessions, are members of the research team (see Counsellors). They are permanently linked to a specific midwifery practice. In this way, all women in the intervention group are assigned to a personal counsellor, facilitating the contact between participant and counsellor. Each counselling session takes 15 minutes, but the first session takes approximately half an hour, to explain the aim of the study and the intervention. The content of the first module is generalised and summarised in an information brochure, which the participants receive after the first counselling session of the intervention program.

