### Measurements

Participants in both the intervention and control group are invited for six measurement appointments in the period during and after pregnancy. The baseline measurement is at 15 weeks of pregnancy. Data are collected at: 15, 25, and 35 weeks of pregnancy and at 8, 26, and 52 weeks after delivery. At these occasions the research assistants perform anthropometrical measurements in all midwifery practices and register the primary outcome measures. Blood samples are collected in five of the eight participating practices by trained assistants; in the other three practices the assistants are not schooled for intravenous punctures and consequently no blood samples can be collected. Each assistant is permanently linked to one or more practices, so that participants are measured by the same person at each occasion. All participants receive questionnaires by ordinary mail one week before each measurement appointment. They are asked to complete the questionnaires and hand these in when they visit the research assistant for a measurement appointment. The assistant personally checks the questionnaires for missing data. The following measures are assessed:

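### The trial is sized on the BMI difference at six months postpartum, but the stated longitudinal coefficient is an average over visits and equals that difference only if the effect is constant over time

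*Protocol article*

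**What the plan says.** **Target of the sample size** (Methods, Sample size). The purpose of the calculation is given as "In order to be able to detect a clinically relevant difference in BMI of 0.8", in units of kg/m². The moment of comparison is fixed as six months after delivery. It uses SD 2.0 kg/m², two-sided 5% and 80% power, and gives 110 women per group, 220 in all, raised to 275 for 20% dropout.

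**Analysis** (Methods, Statistical analyses). Dichotomous outcomes get longitudinal logistic regression and all others get longitudinal linear regression, allowing for correlation within a woman. The estimate is described in one sentence: "The regression coefficient reflects the average difference in the outcome variable between conditions". The only interactions mentioned are for effect modification, judged at p < 0.10, and time is not named among them. Five domains are listed. Pregnancy weight gain and exceeding the IOM guideline are the first two. Weight retention at six months and one year is the third.

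**Visits** (Methods, Measurements). "Data are collected at: 15, 25, and 35 weeks of pregnancy and at 8, 26, and 52 weeks after delivery". The 15-week visit is called baseline. The section on body weight and BMI has the measured values used for BMI at 26 and 52 weeks after pregnancy.

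**Counselling** (Methods, Intervention). For women in the intervention group, "they have appointments with their counsellor at 18, 22, 30 and 36 weeks of pregnancy and at 8 weeks postpartum".

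**The concern.** The sample size refers to one moment, six months after delivery. The analysis section describes one number per outcome that averages over whichever repeated measurements are in the model. The two coincide only if the group difference does not change between those measurements, and nothing in the protocol article supports that. The last counselling contact is at 8 weeks postpartum, so by 26 weeks it lies 18 weeks back and by 52 weeks 44 weeks back. The effect could fade, persist or grow over that period.

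At stake is what the headline result means. A reported average would be read against the 0.8 kg/m² that justified the sample size, although it answers a different question. With no time-specific contrast stated, the choice between an average and a six-month estimate also stays open until data are in hand.

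A smaller fault sits in the same paragraph. Total pregnancy gain and exceeding the IOM guideline are observed once per woman, so there are no repeated measurements for a longitudinal model to handle.

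**Working it through.** **Inputs from the Sample size section:** difference 0.8 kg/m² at six months; SD 2.0; two-sided 5%; power 80%; 110 per group. **Assumed, because the article gives no figure:** within-woman correlation ρ = 0.8 (range 0.7 to 0.9), the same SD at each visit, complete data, and the 52-week effect.

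**1. The plan's own figure.** n per group = 2 × (1.96 + 0.842)² × 2.0² / 0.8² = 98.1, so 99. The stated 110 is larger than its inputs require, which is conservative. The dropout step reproduces: 220 / 0.80 = 275.

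**2. Power of the 26-week contrast at 110 per group.** Standard error = 2.0 × √(2/110) = 0.270. Then 0.8 / 0.270 = 2.97, and Φ(2.97 − 1.96) = 84%.

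**3. The average over 26 and 52 weeks, the narrowest reading.** With balanced data and equal correlation the group coefficient is the mean of the two visit differences. SD of a woman's two-visit mean = 2.0 × √((1 + ρ)/2), which is 1.897 at ρ = 0.8. Standard error = 1.897 × √(2/110) = 0.256. Power = Φ(average / 0.256 − 1.96).

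| Effect at 26 weeks | Assumed effect at 52 weeks | Average | Power, ρ = 0.8 | Power, ρ from 0.7 to 0.9 |
|---|---|---|---|---|
| 0.8 | 0 | 0.40 | 35% | 36% to 33% |
| 0.8 | 0.4 | 0.60 | 65% | 68% to 63% |
| 0.8 | 0.8 | 0.80 | 88% | 90% to 86% |
| 0.8 | 1.2 | 1.00 | 97% | 98% to 97% |

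Only the third row returns the powered quantity. There the average has more power than the single visit, because averaging lowers the variance.

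**4. The same comparison with baseline adjustment.** Take ρ = 0.8 with the 15-week value too. The adjusted SD at 26 weeks is 2.0 × √(1 − 0.8²) = 1.2, and 0.8 / (1.2 × √(2/110)) = 4.94, so power exceeds 99%. For the two-visit mean, the adjusted variance is 3.6 − 3.2²/4 = 1.04, SD 1.02. An average of 0.60 then gives 0.60 / (1.02 × √(2/110)) = 4.36, and power again exceeds 99%. Adjustment removes the power gap, but the estimate is still 0.60 and not 0.80.

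**The case against.** **A generic sentence in a condensed article.** The quoted sentence explains the method across five domains, and visit lists, time coding and contrasts are commonly left to a fuller plan. That is fair for the visit list and for baseline handling, and their absence is not held against the article. But the sentence does more than leave detail open: it says what the estimate is. A fuller plan would have to replace that rule to deliver a six-month difference.

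**No loss of power is shown.** This stands. The direction depends on the 52-week effect, and a constant effect gains power. With baseline adjustment at the assumed correlation, power is ample either way. The point is about which quantity is estimated.

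**A stronger reading that does not hold.** A reader might infer that the coefficient averages all six visits, including 15 weeks, where no effect is possible yet, and weights taken during pregnancy, so that it must dilute the effect. The article does not say so. It calls 15 weeks the baseline, ties measured BMI to 26 and 52 weeks, and lists pregnancy gain apart from postpartum retention. Dilution with loss of power would not be certain even on that reading. Assumed effects of 0, 0.6, 1.2, 1.0, 0.8 and 0.8 average 4.4 / 6 = 0.73. With SD 2.0 × √((1 + 5 × 0.8)/6) = 1.826, power is 85%, about that of the single visit.

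**Once-only outcomes.** With one record per woman, a marginal longitudinal model reduces to ordinary regression. The practical harm is small, but the wording should still be corrected.

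**Conclusion.** The point holds in a limited form. The sample size rests on a six-month difference, and the stated coefficient is an average over repeated measurements with no six-month contrast. On the narrowest reading, with 0.8 at 26 weeks and a 52-week effect between 0.4 and 1.2, the average runs from 0.60 to 1.00 and unadjusted power from about 65% to 97%, against 84%. These figures rest on assumed 52-week effects and an assumed correlation. They show how far the two quantities can part, not which way they will.

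It cannot be concluded that the 15-week visit or pregnancy weights enter any average, or that the effect is diluted. The article leaves the visit list open, and for BMI its text points to the two later postpartum visits. What can be said is that those earlier visits should not enter as outcome visits carrying a treatment effect.

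**What to change.** - For postpartum BMI, body weight and skinfolds, fit the longitudinal model with visit as a category and a group-by-visit term.
- Adjust for the baseline value and for midwifery practice, which is the randomisation stratum. The 15-week value is taken after women are told their group but before the first session at 18 weeks, so call it pre-intervention.
- Name the 26-week postpartum contrast as the primary estimate, to match the sample size, and report the 52-week contrast separately.
- State that the 15-week and later pregnancy visits are not outcome visits in these models.
- Analyse total pregnancy weight gain with ordinary linear regression and gain above the IOM guideline with ordinary logistic regression.

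The cost is a few sentences of analysis text and slightly longer code. No new data, visits or participants are needed.
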